## Abstract

**Background:**

While strong and consistent evidence supports the role of lifestyle modification in the prevention and management of type 2 diabetes (T2DM), the best strategies for program implementation to support lifestyle modification within primary care remain to be determined. The objective of the study is to evaluate the implementation of an evidence-based self- management program for patients with T2DM within a newly established primary care network (PCN) environment.

**Method:**

Using a non-randomized design, participants (total N = 110 per group) will be consecutively allocated in bi-monthly blocks to either a 6-month self-management program lead by an Exercise Specialist or to usual care. Our primary outcome is self-reported physical activity and pedometer steps.

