Acknowledging that gaps still exist in terms of our understanding of real world exemplars of diabetes self-management delivered in primary care, we designed the Healthy Eating and Active Living for Diabetes in Primary Care Networks (HEALD-PCN) study to explore questions around the effectiveness and efficiency of delivering an evidence-based self-management program linked with community resources within in a newly emerging model of primary care. We intend to develop a comprehensive understanding of the system requirements for implementation, which will in turn provide supportive evidence to inform policy makers with respect to resource allocation and the potential for program sustainability.

The main objective of HEALD-PCN is to evaluate a novel implementation of an evidence- based self-management program for patients identified as having T2DM within an established Primary Care Network environment in Alberta, Canada. The primary study hypothesis is that those allocated to HEALD-PCN program will self-report higher levels of moderate and vigorous physical activity and objectively monitored daily pedometer steps. Secondary objectives are to complete a comprehensive evaluation to understand why the program did or did not have an impact, identify critical factors to successful implementation and to develop recommendations to mitigate barriers to successful implementation if the intervention proves effective.

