#### Study measures

We will use a combination of metrics to determine the effectiveness of the HEALD-PCN. As in our HEALD pilot study [23], the primary outcome is physical activity determined by self- report and pedometers. Secondary outcomes include nutrition behaviours (healthy eating and glycemic index), anthropometric assessments, and biomarkers. All primary and secondary outcomes will be collected at baseline, 3 and 6 months, through surveys and point of care instrument testing. Demographic, health/medical and other related characteristics will also be assessed at baseline, 3 and 6 months. At study completion, we will assess self-reported health status and satisfaction with the intervention materials and pedometers. We will also collect information on the cost of this enhanced lifestyle program in the PCN environment and subsequent participant health care utilization, through linkages with Alberta administrative data. To do so, participants enrolled in the study will be asked for permission to access their medical records by signing a consent form and providing their personal health number, thus allowing linkage to Alberta Health and Wellness physician billing, hospital billing, and emergency room billing data. This linkage will allow health care utilization and health care costs to be included in the evaluation.

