##### Physical activity behaviours

Our primary outcome is self-reported physical activity, assessed with the Godin Leisure Time Exercise Questionnaire (GLTEQ) [28], modified to calculate MET minutes values [29] for total moderate and vigorous physical activity. The GLTEQ asks participants to report the average number of times per week, in the past month, they engaged in vigorous (rapid heartbeats, sweating), moderate (not exhausting, light perspiration) and mild (minimal effort and no perspiration) intensity PA, for a minimum of 10 minutes per session. Participant responses for the moderate and vigorous activity categories will be added together to calculate moderate and vigorous physical activity (MVPA) minutes per week and will serve as our primary self-report outcome measure.

For walking specific behaviors, pedometers (Yamax SW-200) and step logs will also serve as an objective measure of our primary outcome. Participants in both the intervention and control groups will be provided with a pedometer, and instructed to wear it and record total daily step-counts in a log for 3 consecutive days including one weekend day. The step log also allows for the collection of brisk steps for the intervention group. Self-reported walking will also be assessed using questions form the International Physical Activity Questionnaire (IPAQ) long version [30]. Participants will be asked, “During the last 7 days on how many days did you walk for at least 10 minutes at a time to go from place to place” or “in your leisure time”. Participants will then be asked, “How much time did you usually spend on ONE of those days walking from place to place” or “walking in your leisure time”. Responses will be recorded in days, hours, and/or minutes per day. A walking score will be calculated by multiplying the number of walking days by the walking minutes then by 3.3 (the MET value suggested for walking) to obtain walking scores in MET-minutes. Stages of physical activity behaviour change measures (≥ moderate levels) initially developed by Reed and colleagues [31] will serve as a secondary behavioral outcome (to assess stage transition).

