### Analytic strategy

All statistical tests will be two-sided with a level of significance set at 0.05 to evaluate the effectiveness of the intervention. Baseline comparisons will be performed using univariate analysis of variance (ANOVA) for continuous variables and chi-square analyses for categorical variables. The main analysis of our study is to compare the physical activity of the HEALD-PCN intervention (On) group participants to the usual care (Off) group, from baseline to 6 months as our primary assessment time-point. Employing the intention-to-treat (ITT) approach, we will also assess differences in group changes from: (1) baseline to 3 months, (2) baseline to 6 months, (3) and 3 months to 6 months using generalized linear mixed-model analysis (GLMM). GLMM uses all available data and provide a valid analysis when data are missing at random. The models will use baseline values for each outcome variable as a covariate to reduce the residual standard error and account for regression to the mean. Potential confounding variables (i.e., age, sex and BMI) will be included as covariates in the models. All data will be analyzed using Statistical Package for the Social Sciences v.20, SPSS Inc., Chicago Illinois, USA and Stata SE 10.1, StatCorp, College Station, Texas, USA.

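### Self-reported MVPA and pedometer steps are both called primary and each is tested at 0.05, with no rule on whether one or both must succeed

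*Protocol article*

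**What the plan says.** Four places in the protocol article define the primary outcome, and they do not agree.

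- Abstract, Method: "Our primary outcome is self-reported physical activity and pedometer steps", which is two measures under one singular label.
- Background, primary hypothesis: the intervention group "will self-report higher levels of moderate and vigorous physical activity and objectively monitored daily pedometer steps".
- Study measures: "the primary outcome is physical activity determined by self- report and pedometers".
- Physical activity behaviours: the first sentence is "Our primary outcome is self-reported physical activity, assessed with the Godin Leisure Time Exercise Questionnaire (GLTEQ", with no pedometer. Weekly MVPA minutes from that questionnaire "will serve as our primary self-report outcome measure". The next paragraph says that pedometers and step logs "will also serve as an objective measure of our primary outcome".

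The Analytic strategy states: "All statistical tests will be two-sided with a level of significance set at 0.05". It makes 6 months the primary time point. The sample size paragraph gives each measure its own calculation at power 0.90 and alpha 0.05: 86 per group for physical activity behaviour (f = 0.25, r = 0.5) and 75 per group for steps (8,250 versus 6,500, SD 3,300). The total is then raised to 110 per group for 20% attrition. The article gives no order of testing, no split of alpha and no rule for combining the two results.

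**The concern.** A reader cannot tell whether steps are co-primary, jointly required or supportive. That choice decides what counts as a positive trial, and the text leaves it open until the data are in.

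The two measures can disagree. MVPA minutes leave out mild activity, while steps count walking at any pace. The first 12 weeks target total daily steps, and faster walking is taught only in weeks 13 and 14, so steps could rise without MVPA. MVPA could also rise without steps, because it is self-reported by people who know which programme they are in. With every test at 0.05 and no rule, success could be claimed on whichever measure is significant.

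**Working it through.** **Inputs.** From the Analytic strategy: two-sided alpha 0.05; power 0.90; f = 0.25, which for two equal groups is d = 2f = 0.5; r = 0.5; a step difference of 1,750 with SD 3,300, so d = 1,750/3,300 = 0.530; 110 per group with 20% attrition, so 110 × 0.8 = 88 per group evaluable. The correlation ρ between the two test statistics is not given. It is assumed and shown over a range.

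**1. The plan's own figures.** With n = 2(1.960 + 1.282)²/d² per group:
- Steps: n = 74.7, rounded up to 75, as stated.
- Physical activity: n = 84.1, rounded up to 85. The exact t-test version gives 86, as stated.

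So 86 matches a plain two-group comparison at d = 0.5.

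**2. If either measure is enough.** The error rate under no effect on either measure is 1 − P(|Z₁| < 1.96 and |Z₂| < 1.96), with Z₁ and Z₂ standard normal and correlated ρ. At ρ = 0 this is 1 − 0.95² = 0.0975.

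| Assumed ρ | Error rate |
|---|---|
| 0 | 0.0975 |
| 0.3 | 0.0951 |
| 0.5 | 0.0907 |
| 0.7 | 0.0835 |
| 0.9 | 0.0704 |

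The rate is above 0.05 at every value shown.

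**3. If both measures are required.** The error rate is at most 0.05, so no alpha correction is needed. What changes is power. The noncentrality is d√(n/2) with n = 88:
- Unadjusted: MVPA 0.5 × √44 = 3.317, power 0.913. Steps 0.530 × √44 = 3.518, power 0.940.
- Adjusted for baseline, as the Analytic strategy plans, taking r = 0.5 as the baseline to follow-up correlation: the residual SD shrinks by √(1 − 0.5²) = 0.866. MVPA 3.317/0.866 = 3.830, power 0.969. Steps, if r = 0.5 also applies, 3.518/0.866 = 4.062, power 0.982.

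Joint power is P(Z₁ < δ₁ − 1.96 and Z₂ < δ₂ − 1.96), where δ₁ and δ₂ are the noncentralities:

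| Model | ρ = 0 | ρ = 0.5 |
|---|---|---|
| Unadjusted | 0.858 | 0.873 |
| r = 0.5 used for MVPA only | 0.911 | 0.919 |
| r = 0.5 used for both | 0.952 | 0.956 |

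All of these treat participants as independent, as the plan's own calculation does.

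**The case against.** **The text leans towards an order.** MVPA is named first, pedometers are said to serve as well, and the step calculation comes second. A detailed multiplicity rule is also commonly left to the SAP, which is not shown. This has weight as a guide to which rule to adopt. It does not remove the point: the identity of the primary outcome is stated in this article, and stated inconsistently, and the article itself sets all tests at 0.05.

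**No passage states an either-is-enough rule.** That is true. The hypothesis joins the measures with an and, which read literally controls alpha. The inflated error rate is therefore conditional: the text permits that reading but does not adopt it.

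**A reader might infer that the trial is underpowered if both measures are required,** because joint power is 0.86 to 0.87 at 88 per group, below 0.90. The article does not support this. It claims 0.90 for each measure separately, and each exceeds that at 88 per group even unadjusted. The 0.86 to 0.87 figure also ignores the planned baseline adjustment. With r = 0.5 used for MVPA alone, joint power is already about 0.91. Taking r = 0.5 as the baseline correlation, and extending it to steps, are assumptions. The first is the natural reading of a design with two time points, and the second is not needed to pass 0.90.

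**MVPA is a doubtful gatekeeper,** being unblinded self-report placed ahead of the measure that the article calls objective. This is a fair point about choice. Participants also write down their own step counts in a log, so the contrast is weaker than it looks. The sequence proposed here is one acceptable rule among several.

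**Conclusion.** The point holds as an inconsistency in the definition of the primary outcome, combined with an analysis that tests each measure at 0.05 without a success rule. If success on either measure is enough, the primary error rate is 0.070 to 0.0975 for assumed test correlations from 0.9 down to 0. A figure of 0.09 to 0.10 applies only up to a correlation of about 0.5.

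A shortfall in joint power is not shown. It appears only in an unadjusted analysis, which is not the planned one. The separate sample sizes of 86 and 75 reproduce and are not in question.

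**What to change.** Make the abstract, the hypothesis in the Background, Study measures, Physical activity behaviours and Analytic strategy state the same rule. Two workable versions:

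1. **Fixed sequence.** Test questionnaire MVPA at 6 months at two-sided 0.05. Test steps per day at two-sided 0.05 as confirmatory only if MVPA is significant. This follows the article's own order, and the 86 per group for physical activity already drives the total. The cost is that steps cannot be claimed as confirmatory if MVPA fails.
2. **Both required.** If the hypothesis is meant literally, state that both must be significant at 0.05. Calculate joint power under the planned baseline-adjusted model and state the correlations assumed. Do not insert 0.86 to 0.87 as the power, because that is the unadjusted figure.

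The first version changes wording only and leaves the sample size alone. The second adds one power calculation.

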**Discussion:**

The present study will assess whether a diabetes self-management program lead by an Exercise Specialist provided within a newly emerging model of primary care and linked to available community-based resources, can lead to positive changes in self-management behaviours for adults with T2DM. Ultimately, our work will serve as a platform upon which an emerging model of primary care can incorporate effective and efficient chronic disease management practices that are sustainable through partnerships with local community partners.

**Clinical Trials Registration:**

ClinicalTrials.gov identifier: NCT00991380

## Background

Globally, 346 million people have diabetes and the prevalence of type 2 diabetes mellitus (T2DM) is expected to increase to an estimated 440 million in the next 20 years [1,2]. Consequently, treating and managing this population will be a substantial burden to health care systems [3]. There is, however, sufficient evidence to suggest that drug treatment, physical activity (PA), medical nutrition therapy, and body weight management can mitigate longer-term complications of diabetes [2] and thus potentially lessen the impending public health burden. Healthy eating and active living are two main ingredients of T2DM self-management. Attention to both nutrition and physical activity (exercise) has repeatedly and consistently been shown to be associated with improvements in metabolic risk [4-7]. As such, guidelines for healthy eating and active living have been developed for use in clinical practice [2,8]. Despite the availability of evidence-based guidelines, the majority of adults with T2DM follow unhealthy dietary patterns and are insufficiently active [9,10] suggesting current frontline approaches to promoting and supporting healthy self-management may not be effective or efficient. Several community-based or ‘real world’ interventions have demonstrated that self-management programs can be effective in improving behavioral and clinical outcomes [11-16]. Although these real world examples have shown success, questions still remain around the longer-term impacts of these interventions at the patient level and at the system level (i.e., primary care setting). More specifically, if patient exposure needs to be increased (i.e., program intensity) to sustain shifts towards positive self-management behaviours seen in what might be considered the early stages of adoption (e.g., 3 months), what are the longer-term costs within the context of sustainability for the patient and, at the same time, within the context of program delivery?

Acknowledging that gaps still exist in terms of our understanding of real world exemplars of diabetes self-management delivered in primary care, we designed the Healthy Eating and Active Living for Diabetes in Primary Care Networks (HEALD-PCN) study to explore questions around the effectiveness and efficiency of delivering an evidence-based self-management program linked with community resources within in a newly emerging model of primary care. We intend to develop a comprehensive understanding of the system requirements for implementation, which will in turn provide supportive evidence to inform policy makers with respect to resource allocation and the potential for program sustainability.

The main objective of HEALD-PCN is to evaluate a novel implementation of an evidence- based self-management program for patients identified as having T2DM within an established Primary Care Network environment in Alberta, Canada. The primary study hypothesis is that those allocated to HEALD-PCN program will self-report higher levels of moderate and vigorous physical activity and objectively monitored daily pedometer steps. Secondary objectives are to complete a comprehensive evaluation to understand why the program did or did not have an impact, identify critical factors to successful implementation and to develop recommendations to mitigate barriers to successful implementation if the intervention proves effective.

## Methods/design

### Ethical approval

All study procedures received approval from the University of Alberta Health Research Ethics Board prior to study commencement. All participants provided written informed consent.

### Setting & population

This research will be carried out in four non-urban Primary Care Networks (PCNs) in Alberta, Canada. All PCNs are stand-alone physician-led corporations established to support family physicians through allied professionals, including: Chronic Disease Management Nurses, Registered Dietitian, Pharmacists, Health Promotion and Prevention Coordinators and Exercise Specialists. According to the Alberta Diabetes Surveillance System, the prevalence of diabetes in the province of Alberta was 5.5% in 2009 with approximately 20% over the age of 65 [17]. In the four participating PCNs, approximately 9,000 adult patients with diabetes are under the care of approximately 140 General Practitioners.

All PCNs in the current study provide some form of basic diabetes group education either through a group-based workshop or one-on-one counseling with a Registered Dietitian and/or Exercise Specialist by physician referral. It is recognized, however that these approaches to support lifestyle self-management are most likely insufficient to achieve and maintain lifestyle changes in the longer term. Thus, the HEALD program is intended to be an enhanced follow-up behavioral support program, prescribed for patients who have already received some form of basic diabetes self-management education. The HEALD-PCN evaluation will be over and above the baseline self-management education through a pragmatic controlled trial [18].

### Study subjects & recruitment

To satisfy the main objectives and achieve the study aims, we propose to implement and evaluate the HEALD program among recently diagnosed patients who are cared for within the PCN environment. One component of the PCNs management structure was the development of a chronic disease patient registry. More generally, a unique PCN patient registry will include information about the patient’s medical management and allow physicians and PCN staff to track patient progress. In keeping with the primary care network patient chronic disease management strategy (i.e., tracking), potentially eligible patients will be identified and recruited through a patient registry.

Following identification of potential study participants through each participating PCN, an endorsement letter from each PCN will be mailed to the potential participant by staff located at each PCN. Staff with this research responsibility within each of the PCN environments is intended to simulate real world chronic disease management practices (i.e., recruitment to available PCN programs). The endorsement letter was selected as a recruitment option after consultation with the PCN chronic disease management teams as a means to create a credible link between the PCN and their clients. Those interested in the study will be asked to contact the PCN by telephone where they will be prescreened to further determine eligibility. For those who have not responded by telephone within a specified time, a PCN staff member will perform a follow up phone call to determine interest and eligibility. Once an individual is deemed eligible, they will be sent a study package, which will include: a study information sheet endorsed by the local PCN physician lead for chronic disease management, a consent form and a pedometer with instructions. A baseline appointment will then be made with a trained Exercise Specialist to collect all relevant baseline clinical/laboratory information at each centralized PCN location using point-of-care instruments.

Inclusion criteria

· On primary care patient registry (i.e., under PCN physician care);

· 18-75 years of age or who are capable of sustained walking for 10 minutes;

· Diagnosed with type 2 diabetes (self-reported and confirmed through PCN patient registry);

· Received basic diabetes education since being diagnosed;

· Proficient English language skills.

Exclusion criteria

· Unable to provide informed consent or unwilling to participate in the study;

· Unable to read, understand, and converse in English;

· Significant cardiovascular contraindications (self-reported history when prompted);

· Significant current depression (self-reported) Patient Health Questionnaire-9;

· Currently enrolled in any other study.

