#### HEALD-PCN intervention

The HEALD-PCN intervention is based on a previously pilot-tested self-management program in this patient population [23]. It consists of two phases, lasting a total of 24 weeks, with emphasis on physical activity (walking) and nutritional elements. During weeks 1 to 12 (phase 1), participants allocated to the intervention group will be placed in a self-monitored, pedometer-based walking program targeting total daily steps. With initial guidance from an Exercise Specialist, each participant will set his or her own daily step goals. A baseline average will be calculated from three consecutive days including one weekend day [23-25] to help participants set individualized goals. The program goal for all participants over the first 12 weeks (phase 1) will be to increase their number of steps/day.

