As part of phase 1, during weeks 1 and 2, participants will attend a 30-minute, group-based meeting, including a supervised walking session, facilitated by the Exercise Specialist, and located at a community recreation facility. A pedometer, a resource manual and step logbook will be provided at the first meeting to facilitate goal setting and to record the total number of steps/day. Access to the community recreation facility is based on partnership arrangements between the research team, the PCN and the local recreation facility management. Financial arrangements for these agreements are provided by the research funding. After week 12 (phase 2), participants will be asked to continue to walk the same number of steps/day that they walked during weeks 10-12 of phase 1. As part of phase 2, during weeks 13 and 14 participants will attend two more group-based meetings at the same community recreation facility, where they will be taught by the PCN Exercise Specialist how to increase their walking speed by 10% during a 30 minute walk. The participants will be asked to incorporate this faster walking pace for 30 minutes/day on 3 days/week on their own, until the end of the study period. For example, if a participants’ self-selected walking pace was 90 steps/minute, they will be encouraged to increase his or hers’ pace to approximately 100 steps/minute. Participants will be asked to perform their faster walking in bouts lasting no less than 10 minutes, and will be given a second pedometer and a stopwatch to help them measure and monitor their brisk steps and time. A second resource manual will be given to accompany this part of the program, which will include a set of small portable cards to record the number of brisk steps immediately after they are performed.

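### The inclusion criterion joins age and walking ability with 'or', so adults aged 18-75 who cannot walk for 10 minutes are eligible and the upper age limit lapses for anyone who can

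*Protocol article*

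**What the plan says.** Under Study subjects & recruitment, the protocol article lists as a single inclusion criterion "18-75 years of age or who are capable of sustained walking for 10 minutes". It is the only eligibility statement on age or on walking ability.

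The exclusion list covers consent and willingness, English, self-reported cardiovascular contraindications, current depression, and enrolment in another study. It mentions neither age nor ability to walk.

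The section HEALD-PCN intervention describes two phases. In the first, intervention participants "will be placed in a self-monitored, pedometer-based walking program targeting total daily steps". In the second they are taught to walk 10% faster and to do so for 30 minutes on three days a week: "Participants will be asked to perform their faster walking in bouts lasting no less than 10 minutes". The abstract gives the endpoint: "Our primary outcome is self-reported physical activity and pedometer steps".

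**The concern.** An eligibility rule should deliver people who can take up what the trial offers. The 10-minute walking condition has the same length as the shortest permitted brisk bout, so it looks designed for that purpose. As written it screens out nobody aged 18-75, because age alone already satisfies the criterion. In the other direction, the ceiling of 75 stops nobody who can walk for 10 minutes.

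Two things are at stake. Some people may enter a walking program whose second phase they cannot follow as described. And the enrolled population is not clearly defined, because a reader can take the sentence in more than one way. Eligibility is pre-screened by telephone at each of four PCNs, so the wording matters in practice.

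**Working it through.** No arithmetic is needed for the main point. It is a check of logic against the rest of the text.

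**Step 1: the criterion as written.** Let A be age 18-75 and W be able to sustain walking for 10 minutes. All other criteria are taken as met.

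| Person | 'A or W' (as written) | 'A and W' (for comparison) |
|---|---|---|
| A, W | eligible | eligible |
| A, not W | eligible | not eligible |
| not A, W | eligible | not eligible |
| not A, not W | not eligible | not eligible |

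The present wording admits two groups that would be left out if both conditions had to hold: people aged 18-75 who cannot walk for 10 minutes, and people outside that age range who can. People unable to walk who are outside the age range are not admitted.

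**Step 2: does another criterion remove either group?** No. Of the five exclusions, only the cardiovascular one bears on physical capacity. It rests on self-reported history and would not cover someone limited in walking for another reason. None concerns age.

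**Step 3: does the rest of the article narrow either group?** For age, partly. The abstract's discussion asks whether the program "can lead to positive changes in self-management behaviours for adults with T2DM", and Setting & population counts adult patients. So although the criterion would literally also admit people under 18, the practical effect is loss of the upper limit. For walking ability, nothing narrows it.

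**Step 4: set the criterion beside the intervention.** Someone in the (A, not W) row can set personal step goals in phase 1, because these start from the person's own baseline. In phase 2 the same person is asked for brisk bouts of a length that, by definition, he or she cannot sustain at any pace. The criterion and the phase 2 instruction do not fit together.

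**Step 5: can the effect on power be sized?** Only by assuming a fraction p who cannot walk for 10 minutes and who gain nothing. The Analytic strategy plans for f = 0.25, which is d = 2f = 0.50 for two groups, and 110 × 0.8 = 88 per group remain after 20% attrition. A simple unadjusted comparison has power Φ(d√44 − 1.96). With baseline adjustment at the planned r = 0.5, d is divided by √(1 − 0.25) = 0.866.

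| Assumed p | d(1 − p) | Power, unadjusted | Power, baseline-adjusted |
|---|---|---|---|
| 0 | 0.50 | 0.91 | 0.97 |
| 5% | 0.475 | 0.88 | 0.95 |
| 10% | 0.45 | 0.85 | 0.93 |

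Whether power falls below the planned 90% depends on the formula, and every row after the first depends on a value of p that the article does not give. These figures are shown to explain why no power loss is claimed.

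**The case against.** The best defence is that the sentence is a slip, or that it was meant as an age exception: 18-75, or older if able to walk for 10 minutes. That reading is plausible in a study that puts external validity first, and the article does not show which rule was intended. This part of the objection stands, and it is a reason not simply to replace 'or' with 'and', which would exclude every able walker over 75. But the age-exception reading explains only one of the two extra groups. People aged 18-75 who cannot walk for 10 minutes remain eligible under it.

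A reader might also infer more than the text supports:

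- **That such participants cannot do the intervention or register on the outcome.** Phase 1 goals are individual and there is a nutrition element. Under Physical activity behaviours, the questionnaire counts any moderate or vigorous activity in sessions of at least 10 minutes, not only walking, and pedometer steps carry no minimum bout. The conflict is with the phase 2 brisk walking in particular.
- **That the trial loses a definite amount of power.** The fraction affected is not given, zero benefit in that group is not established, and the answer changes with the analysis assumed.
- **That people of any age will be enrolled.** The article speaks of adults throughout. What is lost in practice is the limit of 75.
- **That PCNs or allocation blocks will screen differently and bias the comparison.** Allocation is not randomized, so uneven screening would matter if it occurred. But the same criterion applies to both groups, eligibility is settled before allocation, and the pre-screen script is not shown. Nothing in the article shows uneven application.

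**Conclusion.** The point holds as a defect in a stated rule. It is not a matter of detail left to a fuller protocol: the criterion is given, and as given it lets age 18-75 waive the walking condition and lets walking ability waive the upper age limit. It works against the trial's own intervention and is not corrected elsewhere in the article. This conclusion rests only on the ordinary meaning of 'or' and on the eligibility lists as printed.

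Its numerical size is unknown. The planned sample size is unaffected, and no bias or loss of power is shown. It should be corrected because the correction is almost free and the rule decides who is enrolled.

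**What to change.** Split the line into two separate inclusion criteria, one for age and one for walking ability, so that the 10-minute walking condition stands alone and is no longer waived by being aged 18-75. This reconciles it with the two phases described under HEALD-PCN intervention. In the age criterion, the sponsor should state explicitly whether people over 75 who can walk are eligible; that choice is the sponsor's and the article does not settle it. The telephone pre-screen at all four PCNs should carry the same two lines.

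The cost is one line of protocol text and a matching change to the pre-screen form. Slightly fewer people will be eligible, from about 9,000 adult patients with diabetes in the four PCNs, against 2 × 110 = 220 places. No change to the sample size or the analysis is needed.
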